### Follow-up data collection

Detail of the outcomes to be assessed, how they will be measured, and at which timepoints are shown in Table I. Patient-reported outcomes will be assessed using an electronic (online) questionnaire at six and 12 months from initial randomization. If requested, a paper-based version of the electronic questionnaire will be provided. For those who do not respond to the initial questionnaire, a reminder will be sent two weeks later. Telephone and email follow-up will be used, as applicable, to contact participants, and/or their parent/guardian, who do not respond to either the initial or reminder questionnaire. Clinician-assessed outcomes will be assessed at a face-to-face clinic appointment at six months by a blinded physiotherapist, where possible. Participants who do not attend this face-to-face clinic appointment will be contacted by phone by the local site team and a new clinic appointment sent.

### Data management

All data will be processed according to the General Data Protection Regulation (GDPR) and Data Protection Act 2018,^35^ and all documents will be stored safely in confidential conditions. All electronic patient-identifiable information will be held on a secure, password-protected database accessible only to authorized personnel. Paper forms with patient-identifiable information will be held in secure, locked filing cabinets within a restricted area. The processing of the personal data of participants will be minimized wherever possible by the use of a unique participant trial number on trial documents and any electronic databases. Access to participants' personal identifiable data will be restricted to individuals authorized to have access where this is necessary for their role.

### Sample size

The target sample size for the trial is 334 randomized participants (167 in each treatment group) (power analysis and sample size (PASS) v. 13). This will allow detection of a clinically meaningful moderate standardized effect size of 0.4 with a two-sided 5% significance level, 90% power, and allowing for 20% loss to follow-up. The standardized effect size of 0.4 corresponds to a difference of 6.8 points on the GOAL outcome measure,^20^ which ranges from 0 to 100, with a SD of 17. A difference of 6.8 is considered functionally important and achievable by key stakeholders, including patients who provided input in focus groups, and clinicians we surveyed in preparation for the trial. SDs of this magnitude have been reported in similar patient populations.^20,36^ The sample size assumptions will be reviewed after approximately 50% of the participants have been recruited.

### Statistical analysis

The primary analysis will use the randomized (intention-to-treat (ITT)) population, analyzing participants with available outcome data in their randomized groups, regardless of adherence to their allocated intervention. Primary and secondary outcome analyses will use two-sided 5% significance and 95% CIs with associated p-values.

Differences in GOAL scores between the trial groups will be estimated using a multilevel mixed effects regression model, allowing for repeated measures clustered within participants and for potential clustering within randomizing sites. The model will be adjusted for minimization factors (sex (male, female), anatomical disease distribution (bilateral compared with unilateral CP), and GMFCS level (levels I and II compared with III)), and other important prognostic factors (i.e. neurological pattern, epilepsy, or visual impairment), including the baseline GOAL scores. A treatment by time interaction will be included, indicating the protocol stipulated follow-up time to which the assessment refers. Model diagnostics, including approximate normality of the residuals, will be assessed. Adjusted mean differences and unadjusted mean differences between groups will be presented together with 95% CIs.

We will explore the effect of non-adherence with the randomized interventions using complier-average causal effect (CACE) analyses. Adherence will be defined as having completed all six physiotherapy sessions. However, the treating physiotherapist may decide that treatment is complete over a smaller number of sessions depending on the progress of the adolescent. Secondary outcomes will be analyzed using generalized linear models, with model adjustment as described for the primary analysis above. Subgroup analysis using predefined subgroups will investigate potential outcome predictors such as sex, anatomical distribution of the condition, GMFCS level, or other baseline characteristics. A statistical analysis plan (SAP) with full details of all analyses planned for the study data will be drafted early in the trial and finalized prior to any primary outcome analysis.

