### Randomization

Consented participants will be randomized (1:1) to either the intervention or control group using the REDCap randomization system (a centralized validated computer randomization programme). Randomization will be performed using a minimization algorithm (including a random element) to ensure balance between the two groups using the following minimization factors: centre, sex, anatomical CP distribution (bilateral vs unilateral), and GMFCS (levels I and II compared with III).

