To support adherence to the progressive resistance exercise programme, participants will have access to written instructions on the progressive resistance exercises chosen, including photos of each exercise and video instructions of the progressive resistance exercises chosen via the ROBUST study intervention website.^33^ To ensure accessibility, if families do not have ready access to a mobile device at home, then a device will be loaned to participants to enable them to use the digital intervention during the supervised exercise period. The intervention design and long-term behaviour change implementation have been underpinned by the capability-opportunity-motivation model of behaviour (COM-B) change for intervention development.^18^ The programme includes goal-setting and exercise diaries accessed via the intervention website, with joint problem-solving, monitoring, and motivation from the physiotherapist. The goal-setting and exercise diaries are for use between the participant and their physiotherapist, and will be reviewed at each physiotherapy session.

Usual NHS care: adolescents randomized to usual care will attend for a single session with a physiotherapist for an assessment, lasting up to 90 minutes. This will be in addition to physiotherapy appointments that they receive through their routine clinical care. Appointments will be coordinated so that participants typically receive their assessment session within two to four weeks of randomization, as per local appointment availability. To avoid contamination, where possible, physiotherapists delivering usual care will be different to those delivering the progressive resistance exercise programme. Participants and their parent/carer will be provided with NHS advice on self-management, including a participant information booklet on exercise and activity for young people with CP and continuation of any usual fitness/physical activity programme (as applicable).^19^

Participants allocated to the usual care group will not have access to the progressive resistance exercise programme. Usual care will be recorded using a treatment log maintained on the REDCap trial website by the trial physiotherapists. A guideline on what is considered ‘usual NHS care’ will be provided to the physiotherapists delivering it, and they will be trained to understand the components of this, to ensure they know the boundary of provision.

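### The primary model names no treating-therapist or site-by-treatment term, so if outcomes vary by physiotherapist the confidence interval for the treatment effect may be too narrow

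*Protocol article*

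**What the plan says.** The Statistical analysis section of the protocol article specifies a multilevel mixed effects regression for GOAL, "allowing for repeated measures clustered within participants and for potential clustering within randomizing sites". Two levels are named: participant, for the repeated measures, and randomizing site. Baseline GOAL is a covariate. Full details are deferred to a statistical analysis plan.

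The Interventions section gives the active arm six one-to-one sessions over 16 weeks. The exercises are chosen jointly with the physiotherapist, who also supports problem-solving and motivation. The usual care arm has a single trial session. To limit contamination, and where possible, "physiotherapists delivering usual care will be different to those delivering the progressive resistance exercise programme".

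The Sample size section gives the target and its basis: "The target sample size for the trial is 334 randomized participants (167 in each treatment group"), with "two-sided 5% significance level, 90% power, and allowing for 20% loss to follow-up". The effect is stated as follows: "The standardized effect size of 0.4 corresponds to a difference of 6.8 points on the GOAL outcome measure", "which ranges from 0 to 100, with a SD of 17". No ICC, caseload or design effect is given. The assumptions are to be reviewed at about 50% recruitment.

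**The concern.** In the active arm the physiotherapist is part of the treatment, so adolescents treated by the same therapist may have more similar outcomes than adolescents treated by different ones. Keeping the two groups of therapists apart nests therapist within arm within site.

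The site level does not deal with this. Centre is a minimization factor, so both arms are represented at each site in roughly equal numbers, and an additive site effect largely drops out of the difference between arms. A therapist effect present in one arm stays in that difference. The participant level does not help either, because it describes correlation within one adolescent over time.

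At stake is the validity of the primary inference. An omitted variance component of this kind is anti-conservative: it makes the standard error too small and a false positive claim of superiority more likely.

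**Working it through.** **Inputs from the protocol article.** Standardized effect 0.4 (6.8/17), two-sided 5%, 90% power, 20% loss, 1:1 allocation and 334 randomized (Sample size, Randomization); at least 12 NHS Trusts (Setting).

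**Assumed, because the protocol does not give them.** Therapist ICC 0.02 or 0.05; 12 intervention therapists (one per site at the minimum number of sites) or 24; clustering in the intervention arm only; every therapist treating one arm only.

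**Step 1: reproduce 334.** A two-sample t-test on independent observations needs 133 per arm (power 0.9015). 133/0.8 = 166.25, so 167 per arm and 334 in total, an exact match. The design effect in the stated calculation is therefore 1.

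**Step 2: effect on the standard error and test size.**
- Analysed per arm: 167 × 0.8 = 133.6.
- Caseload: m = 133.6/12 = 11.13, or 133.6/24 = 5.57.
- Design effect in the intervention arm: DE = 1 + (m − 1) × ICC.
- True SE divided by reported SE: f = √((DE + 1)/2).
- Actual error of the nominal 5% test: 2 × (1 − Φ(1.96/f)).
- Power on the unadjusted basis of the sample size: Φ(0.4 × √(133.6/2)/f − 1.96) = Φ(3.269/f − 1.96).

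| Therapists | ICC | DE | f | Actual error | Unadjusted power |
|---|---|---|---|---|---|
| 12 | 0.02 | 1.203 | 1.05 | 6.2% | 88% |
| 12 | 0.05 | 1.507 | 1.12 | 8.0% | 83% |
| 24 | 0.02 | 1.091 | 1.02 | 5.5% | 89% |
| 24 | 0.05 | 1.228 | 1.06 | 6.3% | 87% |

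A simulation with 12 sites, 11 analysed per arm at each site and an additive site effect gave 6.4% and 7.8% for the two 12-therapist rows (6,000 replicates), in line with the formula.

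**Step 3: credit for baseline adjustment.** The primary model adjusts for baseline GOAL and the sample size does not. Assume a baseline correlation of 0.5, which leaves 1 − 0.25 = 0.75 of the variance in each arm, and keep the therapist variance at its full size. In units of the outcome SD:
- Variance of the difference = (0.75 + 0.75 + (m − 1) × ICC)/133.6.
- 12 therapists, ICC 0.02: (1.5 + 0.203)/133.6 = 0.01275, SE 0.1129, power Φ(0.4/0.1129 − 1.96) = 94%.
- 12 therapists, ICC 0.05: (1.5 + 0.507)/133.6 = 0.01502, SE 0.1226, power Φ(0.4/0.1226 − 1.96) = 90%.

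So, on that assumption, the power margin from the baseline covariate covers the loss from therapist clustering. It does not repair the test size. The ratio of true to reported SE becomes √(1.703/1.5) = 1.07 or √(2.007/1.5) = 1.16, no better than before adjustment.

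**The case against.** The strongest objection is that this is a condensed article. It speaks of potential clustering within sites without naming a random intercept, and it leaves detail to an analysis plan that is not shown. That plan could contain a therapist term, or could read the site clustering as including a site-by-treatment effect. This stands in part: the final model may be better than its summary. But the article does state its clustering levels, and the treating therapist is not among them, so a plan written to match the article would leave it out.

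The second objection is that therapist variance may be small. Most exercise is done at home three times a week. Exercises come from a shared library with load set on a common exertion scale. Therapists have a manual, training and fidelity checks, and GOAL is reported by the child or parent after the 16-week programme has ended. Separation of therapists is only where possible, and therapists who treat both arms would weaken the problem. All of this stands. It is why the consequence is conditional, and why the milder cell (24 therapists, ICC 0.02: 5.5%) belongs beside the others.

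A reader might also infer from the 83% to 89% in the table that the trial is underpowered. The documents do not support that. Those figures are on the unadjusted basis of the sample size, and a baseline correlation of 0.5 would bring power to about 90% or more in the 12-therapist cases. Nor do the documents support saying that the interval will be too narrow, since that requires a therapist variance above zero, which they neither state nor exclude.

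**Conclusion.** The point holds in conditional form. As stated, the primary model has no term that carries variation between treating therapists into the standard error of the treatment contrast, although the delivery plan keeps therapists apart by arm as far as it can. If such variation exists, the interval is too narrow and the p-value too small. For ICCs of 0.02 to 0.05 in the intervention arm, actual error is 6.2% to 8.0% with 12 therapists and 5.5% to 6.3% with 24. It would be lower if some therapists treat both arms, and higher if usual care were also clustered by therapist.

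The stated 90% power rests on independent observations. That assumption should be disclosed, but it is not a demonstrated shortfall. This is an inexpensive improvement to the primary model, not an error in a stated figure.

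**What to change.** 1. Record an identifier for the treating physiotherapist on the REDCap treatment log, which the trial physiotherapists already keep. Do this now, because it is hard to recover later.
2. Add to the primary model a therapist random effect that applies in the intervention arm (a partially nested mixed model). Where a site has one intervention therapist, a site-by-treatment random effect does the same work. Use a small-sample degrees-of-freedom correction, since the number of therapists may be small.
3. State in the Sample size section that the 90% power assumes no therapist clustering. Revisit the assumption, together with the credit from baseline GOAL, at the review already planned at about 50% recruitment.

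The cost is one data field, a change of model wording in the protocol and analysis plan, and a slightly wider confidence interval. No more patients are needed.

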### Missing data

Missing data will be reported and summarized by group. The distribution of missing primary outcome data will be explored to assess the assumption of data missing at random. The potential impact of informative missing data (missing not at random) on the treatment effect will be investigated.

## Ethics and dissemination

Ethical approval was obtained from the South Central – Hampshire A Research Ethics Committee (REC: 23/SC/0231) and prospectively registered (ISRCTN 68282588. A data safety and monitoring committee has been appointed to independently review data on safety, protocol adherence, and recruitment in accordance with the Data Monitoring Committees: Lessons, Ethics, Statistics (DAMOCLES) charter.^37^ Direct access to research data will be granted to authorized representatives of the sponsor (University of Oxford, UK), regulatory authorities, or the host institution for monitoring and/or auditing of the trial to ensure compliance with regulations. Summary results will be included on the ISRCTN database within six months of the end of the trial. Requests for data (anonymized trial participant level data) will be provided at the end of the trial to external researchers who provide a methodologically sound proposal to the trial team (and who will be required to sign a data sharing access agreement with the sponsor) and in accordance with the National Institute for Health and Care Research (NIHR) guidance.

Trial findings will inform clinical practice for the management of ambulant adolescents with spastic CP and its results will be published in a high-impact open-access journal, in accordance with the NIHR’s policy on open-access research. The trial results will be reported following the CONSORT guidelines.^38^ We will use the TIDieR Statement for reporting the intervention,^29^ ensuring that replication is possible. Trial materials, including the physiotherapist training materials and intervention materials, will be made freely available via the trial website. Participants and their parent/guardian will be asked if and how they would like to be informed of the results as part of the consent process.

## Strengths and limitations

The ROBUST trial is a large multicentre RCT based across UK NHS hospital and community paediatric physiotherapy services. Using a two-arm, parallel group, pragmatic design, we will test the effectiveness of an individually tailored strengthening programme, including progressive resistance exercises and advice, overseen by a physiotherapist compared to usual NHS care in ambulant adolescents with spastic CP. The intervention has been designed to ensure deliverability within the NHS setting. Young people and their families were involved in the trial development, including development of the intervention, the creation of the trial materials, and choice of the primary outcome. It is not possible to blind the study participants or physiotherapists delivering the intervention.

**Take home message**

- Muscle strengthening exercises are one of the interventions frequently prescribed by physiotherapists for adolescents with cerebral palsy (CP).

- However, there is wide variability in the exercise regimes used and limited evidence of their effectiveness.

- This article describes the protocol for the ROBUST trial, which is a multicentre trial looking at the clinical effectiveness of an individually tailored strengthening programme, including progressive resistance exercises and advice, compared to usual care for ambulant adolescents with spastic CP.

## Data Availability

The data that support the findings for this study are available to other researchers from the corresponding author upon reasonable request.
